### Sample size calculation and statistical considerations

The literature on the clinical impact of additional liver MRI in patients with primary or recurrent CRLM is very limited and consists of primarily small retrospective studies [26, 35]. Our estimate of the chances of finding CS-CRLM on liver MRI is based on literature, clinical experience and practicality.

A smaller change in local therapy plan is expected than previous studies have shown, as CT technique and interpretation have evolved. Based on these considerations, the proportion of patients in which liver MRI finds CS-CRLM is postulated to be 10%. Such a proportion can be considered as a relevant impact on local therapeutical management.

The primary outcome measure, the proportion of patients with CS-CRLM on liver MRI not identified on CT, guides the sample size for this incremental diagnostic accuracy study. Taking into account that all patients will undergo CT and liver MRI, precision is defined as one-sided 95% confidence interval (CI) with a lower confidence bound of 6.5%. Sample size calculation indicated that 270 patients need to be included in order to obtain estimates of change in management in 10% with 95% CIs that does not exceed 7%.

A small subset of the patients will undergo FDG-PET-CT instead of CT. During a recent national meeting of the Dutch Liver Collaborative Group, an assessment about the use of FDG-PET-CT was performed and approximately 5% of patients in this study is expected to undergo FDG-PET-CT instead of CT. To adjust for patients that undergo FDG-PET-CT instead of CT, an increase of 5% of the desired number of participants is made, resulting in 284 patients. Given the design of the study, a maximum dropout of 5% is expected. Taken this dropout into account, a total of 298 patients must be enrolled in this study. If a participant withdraws consent, a new one will be recruited.

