## Background

Colorectal cancer is the third most common cancer and the second most common cause of cancer related death worldwide [1]. Approximately 30% of patients with colorectal cancer present with colorectal liver metastases (CRLM) or will develop CRLM during follow-up [2–4]. Surgery is the cornerstone of curative intent therapy for these patients with 5-year survival exceeding 40% [3, 5, 6]. In recent years, local ablative techniques are increasingly performed to treat small CRLM showing comparable long-term outcomes to surgical resection in these selected patients [7–11]. Both surgery as well as thermal ablation require accurate detection of CRLM. Therefore, optimal pre-interventional localization of CRLM is of utmost importance to determine an adequate local therapy plan.

The current routine diagnostic workup of patients with suspected CRLM consists of contrast-enhanced computed tomography (CT) [12–14]. While CT provides adequate whole-body staging and has a sensitivity of 70–90% for CRLM lesions of more than 10 mm, the reported sensitivity of CT in the detection of small CRLM (≤10 mm) ranges from 22 to 68% [15–17]. This suggests that CT might not be the optimal diagnostic tool to characterize small liver lesions. In recent years, magnetic resonance imaging (MRI) and positron emission tomography CT with fluorine 18 fluorodeoxyglucose (FDG-PET-CT) have been used in addition to CT to increase accuracy [18–20]. Previous studies reported a lower sensitivity (74.1% vs. 82.1%) of FDG-PET-CT and a higher specificity (93.9% vs. 73.5%) as compared to CT [21]. A recent multicentre randomized trial demonstrated that FDG-PET-CT resulted in a modest change in surgical management of only 8.7%, not meeting the predefined minimum incremental diagnostic accuracy of 25% in that study, without an effect on overall survival [22].

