Although previous literature suggests that liver MRI is superior in detection and characterization of CRLM compared to CT, it is not known whether the higher diagnostic accuracy of MRI has sufficient impact on patient management in terms of additional clinically significant CRLM (CS-CRLM) that actually change the local therapy plan. The current European Society for Medical Oncology (ESMO) consensus guideline for the management of patients with metastatic colorectal cancer recommends the use of MRI in the pre-interventional workup of CRLM, but indicates that more evidence is needed to address the clinical added value of MRI in patients with CRLM [14]. In addition, the American College of Radiology (ACR) Appropriateness Criteria—Pretreatment Staging of Colorectal Cancer highlighted the difficulty to determine the best imaging modality for patients with CRLM because very few studies have adequately compared the accuracy of MRI to high-quality CT [13]. Since the available evidence supports that both MRI and CT detect liver lesions with high accuracy, the ACR Appropriateness Criteria state that CT or MRI may be used to stage CRLM [13]. These inconclusive guideline recommendations stress the lack of robust data and thorough scientific evidence in this field. Hence, the actual role of liver MRI for management of patients with CRLM remains unclear. Until now, no definitive evidence has been provided on the impact of liver MRI on finding CS-CRLM as compared to CT for patients with primary or recurrent CRLM.

The aim of the present CAMINO study is to evaluate whether diffusion-weighted and gadoxetic acid enhanced liver MRI has sufficient clinical added value to CT in order to be routinely performed in the staging of CRLM. This is an international multicentre prospective diagnostic accuracy study assessing the proportion of patients with CRLM scheduled for local therapy in which liver MRI finds additional CS-CRLM as compared to CT. The hypothesis is that the higher accuracy of liver MRI will lead to finding of at least 10% additional CS-CRLM compared to CT, resulting in improved decision-making on the local therapy plan, such as additional surgery or ablation and potentially preventing unnecessary surgical exploration or ablative treatment. The secondary aim of this study is to identify subgroups which benefit most from additional liver MRI.

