### Objectives and hypotheses

The main objective of this study in patients with CRLM is to identify the proportion of patients in which liver MRI including DWI and gadoxetic acid enhanced T1-weighted sequence finds CS-CRLM in addition to an abdominal portal venous phase CT. CS-CRLM are defined as liver lesions that have not been incorporated in the initial resection and/or ablation plan based on CT, hence leading to a change in local therapy. Change in local therapy is defined as any change in surgery or thermal ablation including increase or decrease of the number or extent of liver resections, increase or decrease in number of ablation zones, surgery to ablation, ablation to surgery, addition of ablation to surgery and cancellation of local therapy. The local therapy plan proposed by the MDT based on CT only will be compared to the local therapy plan based on CT and liver MRI. It is hypothesized that liver MRI will lead to the detection of CS-CRLM in at least 10% of patients which is considered the minimal clinically important difference. The findings of this study – whether or not liver MRI including DWI and gadoxetic acid enhanced T1-weighted sequence has clinical added value on local therapy strategy of CRLM patients – will determine the role of liver MRI in the staging of CRLM and will provide international guidelines with data for a scientifically based recommendation on the implementation of liver MRI in the pre-interventional workup.

The secondary aim is to identify which subgroups benefit most from the additional liver MRI by performing a logistic regression analysis and developing a clinical prediction model.

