### Statistical analysis plan

Since the CAMINO study has a pragmatic design and should represent daily clinical practice, the main analysis of the primary outcome will be based on the intention-to-imaging (ITI) population. The ITI population will consist of all included patients fulfilling the inclusion criteria of the CAMINO study, regardless of any study protocol violation such as an extended time interval of more than 4 weeks between CT and MRI and liver MRI performed with another contrast agent then Gadoxetic acid. The incremental accuracy in the ITI analysis will be calculated as the number of included participants with a clinically significant CRLM (CS-CRLM) detected by liver MRI and not seen on CT, as identified by the local MDT, relative to the total number of included participants.

Additionally, the main analysis will be complemented by an imaging-per-protocol (IPP) analysis. The IPP population will include all patients fulfilling the inclusion criteria and undergoing all study procedures per study protocol, excluding patients who showed any study protocol violation or deviation. The incremental accuracy in the IPP analysis will be calculated as the number of included participants with a clinically significant CRLM (CS-CRLM) detected by liver MRI and not seen on CT, relative to the total number of included participants without .

Three subgroup analyses will be performed: first, in the groups of patients who did and did not receive preoperative chemotherapy; second, in patients who did and did not undergo a FDG-PET-CT, and at last, based on the number of CRLM.

A prediction model will be developed using multivariable relaxed lasso logistic regression modelling, to evaluate the probability based on patient, tumor and procedural variables of finding CS-CRLM on liver MRI. This exploratory model will be used for identifying subgroups in whom the probability of finding CS-CRLM is less than 10%. All baseline variables will be considered for the regression model.

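### Planning value and minimal clinically important difference are both 10%, and the size buys only a lower bound of about 7%, so near the planning value it does not support confirming the hypothesis of at least 10%

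*Protocol article*

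**What the plan says.** In the protocol article, Objectives and hypotheses states that "liver MRI will lead to the detection of CS-CRLM in at least 10% of patients which is considered the minimal clinically important difference". The Background words the hypothesis as the "finding of at least 10% additional CS-CRLM compared to CT". The Statistical analysis plan section uses the same figure as a cut-off for the prediction model, which serves for "identifying subgroups in whom the probability of finding CS-CRLM is less than 10" percent.

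The Sample size section then takes 10% as the expected value ("the proportion of patients in which liver MRI finds CS-CRLM is postulated to be 10" percent). It sets the size by precision: "precision is defined as one-sided 95% confidence interval (CI) with a lower confidence bound of 6.5" percent. The next sentence gives 270 patients as the number needed to obtain "estimates of change in management in 10% with 95% CIs that does not exceed 7" percent. Increases of 5% for FDG-PET-CT and 5% for dropout bring the total to 284 and then 298.

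The primary result is defined as a proportion of included participants. Objectives and hypotheses says that the findings will determine the role of liver MRI in staging, and the Discussion says that the study will supply the evidence needed to decide on routine use.

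**The concern.** One number does three jobs: expected value, hypothesised minimum and minimal clinically important difference. When the expected value lies on the threshold, an interval around the expected result must extend below that threshold. The precision target accepts this openly, since it allows values of 6.5 to 7%, about a third below the minimum that is called important.

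The study is presented as settling whether MRI should be routine. If the planning assumption is right, the most likely result is an estimate near 10% with an interval that covers both sides of 10%. Such a result neither confirms nor refutes the hypothesis. Unless this is said beforehand, an estimate of 9.5% or 10.5% can be presented as success or failure once the data are seen.

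**Working it through.** **Inputs.** From the Sample size section: expected proportion 0.10; one-sided 95% (z = 1.645); lower bound 6.5% or 7%; n = 270, 284, 298. From Objectives and hypotheses: minimum of 10%. True proportions above 10% are assumptions, because the article gives none.

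**1. Reproducing 270.** Formula: n = z² p(1−p) / d².
- Lower bound 7.0% (d = 0.03): 2.706 × 0.09 / 0.0009 = 270.6. This is the stated 270.
- Lower bound 6.5% (d = 0.035): 2.706 × 0.09 / 0.001225 = 198.8, so 199. This is not 270.
- Inflation: 270 × 1.05 = 283.5, giving 284; 284 × 1.05 = 298.2, giving 298.

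**2. What an observed 10% would show.** Lower bound = 0.10 − 1.645 × √(0.09/n).
- n = 270: 0.10 − 1.645 × 0.01826 = 0.0700.
- n = 298: 0.10 − 1.645 × 0.01738 = 0.0714.

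Values below about 7% are excluded. Values from 7 to 10% are not.

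**3. Count needed for a lower limit of at least 10%.** By the exact (Clopper-Pearson) limit, the smallest x must satisfy P(X ≥ x | n, 0.10) ≤ 0.05.
- n = 270: x = 36 (13.3%), tail probability 0.047.
- n = 298: x = 40 (13.4%), tail probability 0.035.

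With Wald or Wilson limits the counts are 36 to 37 of 270 and 39 to 40 of 298 (13.1 to 13.7%).

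**4. Chance of reaching that count** (exact binomial, exact limit):

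| True proportion | n = 270 | n = 298 |
|---|---|---|
| 10% (planned) | 4.7% | 3.5% |
| 12% | 28% | 25% |
| 13% | 46% | 44% |
| 14% | 65% | 64% |
| 15% | 80% | 80% |
| 16% | 90% | 90% |

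Over n = 270, 284 and 298 and all three interval methods, the chance is 0.03 to 0.06 at a true 10% and 0.75 to 0.85 at a true 15%.

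**5. Would more patients help?** For 80% power, n = [(1.645 √(0.10 × 0.90) + 0.842 √(p(1−p))) / (p − 0.10)]². At p = 0.15 this is [(0.4935 + 0.3007) / 0.05]² ≈ 253. At p = 0.13 it is 670 and at p = 0.12 it is 1471. At p = 0.10 the denominator is zero, and the chance stays at about the 5% error rate whatever the size.

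**6. The other side.** By the exact limit, the upper limit is below 10% when P(X ≤ x | n, 0.10) < 0.05. For n = 270 this holds up to x = 18 (0.037; 0.059 at 19). For n = 298 it holds up to x = 21 (0.049; 0.075 at 22). Results from 19 to 35 of 270, or 22 to 39 of 298, are compatible with both sides of 10%.

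**The case against.** The strongest reply is that this is an estimation study. Sizing a single-arm incremental-yield study so that an expected 10% has a lower bound near 7% is a recognised approach, and a minimal clinically important difference may be a target for the estimate and need not be a null value. That is right, and the design is not faulted for it. Requiring a lower limit of at least 10% is one strict convention. What remains is that the article also states a directional hypothesis and promises a decision on routine use, and the precision it buys does not reach that far. If the point estimate alone were the yardstick, a true 10% would give an observed value of at least 10% with a chance of only 0.53, 0.48 or 0.51 (n = 270, 284, 298).

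A second reply is that this is a condensed article, and the reading of the interval may stand in the full protocol or a statistical analysis plan. That also stands: the absence of a decision rule is not the point here. The point rests on the printed 10%, 10% and 6.5 to 7%. No later rule could make a lower limit of at least 10% likely at a true 10%.

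A reader might infer three stronger things that the article does not support:
- **That success will be judged against 6.5%.** Under such a rule 25 of 270 (9.3%) would pass. But 6.5% is stated as a precision input, and nowhere as a success criterion.
- **That the study cannot show its hypothesis at all.** At a true proportion of about 15% it probably would. The article sets its 10% below what earlier studies showed, so higher values are not ruled out.
- **That the bound is discredited by the FDG-PET-CT trial, which "resulted in a modest change in surgical management of only 8.7" percent.** That figure is a point estimate for another modality, set against that trial's own 25% minimum. It is not comparable with a confidence bound here.

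**Conclusion.** The point holds in a limited form. The size does not support confirming a proportion of at least 10% if the truth is at or near the 10% on which the study was planned: the chance is about 3 to 6%. It rises to about 80% only at a true proportion of about 15%. These figures assume one-sided 95% limits, independent patients, and a reading in which confirmation means a lower limit of at least 10%.

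Data collection, the primary estimate and its interval are unaffected. What changes is what the study may claim, so this is worth correcting but does not undermine the design. The mismatch between 6.5% and 270 is a separate inconsistency. It matters here only because the sentence on precision should carry the figure that the size delivers.

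**What to change.** No change in enrolment or procedures.

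1. **Sample size calculation and statistical considerations.** State that at an observed 10% with 270 patients the one-sided 95% lower bound is about 7.0%, and correct the 6.5%, which does not give 270. Say that the study estimates the proportion and, at that result, can exclude values below about 7%. Add that about 80% chance of a lower limit of at least 10% needs a true proportion of about 15%, marked as an assumption.
2. **Objectives and hypotheses, Statistical analysis plan, and Sample size.** State that the estimate will be reported with its confidence interval against 10%, read in three ways:
   - at least 10% confirmed, only if the one-sided 95% lower limit is at least 10% (about 36 of 270 or 40 of 298);
   - below 10%, only if the one-sided 95% upper limit is below 10%;
   - otherwise, compatible with both.
3. Name the interval method, since the required count shifts by one patient between methods.

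The cost is a few sentences and a less favourable statement of the study's capability: near the planning value, the likely conclusion is the third.

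### The precision target stated for n = 270 (one-sided 95% lower bound of 6.5%) does not give 270; the figure fits a 7% bound, and the next sentence leaves the meaning of 7% unclear

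*Protocol article*

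**What the plan says.** All the figures are in the protocol article, section 'Sample size calculation and statistical considerations'.

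- Expected value: "the proportion of patients in which liver MRI finds CS-CRLM is postulated to be 10"%.
- First precision statement: "precision is defined as one-sided 95% confidence interval (CI) with a lower confidence bound of 6.5"%.
- Second precision statement, in the next sentence, which gives the purpose of the base number of 270: "obtain estimates of change in management in 10% with 95% CIs that does not exceed 7"%. It does not say whether the interval is one- or two-sided, or whether 7% is a bound or a width.
- Inflation: for FDG-PET-CT, "an increase of 5% of the desired number of participants is made, resulting in 284 patients"; then "a maximum dropout of 5% is expected", so that "a total of 298 patients must be enrolled in this study".

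The article gives no formula, interval method or power. Separately, 'Objectives and hypotheses' sets a clinical benchmark for the primary outcome: "CS-CRLM in at least 10% of patients which is considered the minimal clinically important difference".

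**The concern.** Two adjacent sentences justify one number, yet they give different percentages and only the first states a sidedness. A reader who takes the first sentence literally and computes the sample size gets a number well below 270.

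This passage is the only stated basis for the sample size, and the only place in the article that attaches a confidence bound to the primary outcome. As written, a reader cannot tell what precision 270 patients are meant to deliver, or whether the primary interval should be reported one- or two-sided.

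**Working it through.** **Inputs.** p = 0.10, the two precision statements, 270 and the two 5% increases, all from the sample size section. Assumption: the Wald formula for a single proportion, since the article names none. One-sided 95% uses z = 1.64485; two-sided 95% uses z = 1.95996.

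**Formula.** n = z² p(1 − p) / d², with p(1 − p) = 0.09 and d the distance from 10% to the limit.

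**Reproducing 270.** One-sided 95%, d = 0.03 (lower bound 7%): 1.64485² × 0.09 / 0.03² = 270.55. This is the closest match; strict rounding up gives 271.

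**The criteria as worded**

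| Reading | d | n before rounding | n |
|---|---|---|---|
| One-sided, lower bound 6.5% (first sentence, literally) | 0.035 | 198.8 | 199 |
| One-sided, lower bound 7% (7% as a bound) | 0.030 | 270.55 | 271 |
| Two-sided, 6.5% to 13.5% (7% as a total width) | 0.035 | 282.2 | 283 |

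**What 270 patients deliver at 27/270.** SE = √(0.09/270) = 0.01826.

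- One-sided 95% lower limit: 0.10 − 1.64485 × 0.01826 = 0.0700, that is 7.0%, not 6.5%.
- Two-sided 95% interval: 0.10 ± 1.95996 × 0.01826 = 6.42% to 13.58%, width 7.16 points, just over 7.

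**Does another interval method rescue 6.5%?** Ten methods were tried, including Wald with continuity correction, Wilson, Clopper-Pearson and Jeffreys. The n for a 6.5% lower limit at 10% observed runs from 135 to 227 one-sided and from 191 to 311 two-sided. None falls within 3% of 270 (262 to 278). Read as a one-sided 5% test of 6.5% against 10%, 270 patients would have about 69% to 71% power, but the article states no power, and 80% would need 354.

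**Inflation.** 270 × 1.05 = 283.5, so 284; 284 × 1.05 = 298.2, so 298. Both steps reproduce, so the fault lies in the precision statement alone.

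**At the enrolment target.** With n = 298 and 10% observed, the one-sided Wald lower limit is 7.1% and the two-sided interval is 6.6% to 13.4% (width 6.8 points). 298 exceeds 199, 271 and 283.

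**The case against.** The best defence is that an interval that does not exceed 7% most naturally refers to width. A 7-point width centred on 10% runs from 6.5% to 13.5%, so its lower limit is exactly the 6.5% of the sentence before. The two sentences then describe one interval, and the fault is the label one-sided plus a small shortfall (283 against 270). This is a fair reading, and it means that a flat contradiction between the bounds cannot be asserted. It does not rescue the text: the sidedness is then wrong, and 270 still does not give the stated width. That 270 was computed from a one-sided 7% bound is likewise an inference from the close match, since no formula is shown.

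Two stronger conclusions are tempting, and the documents support neither.

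- *A reader might infer that the trial is too small.* 270 is more than the literal first criterion requires, and 298 covers all three Wald readings. Other targets can be built that 298 would miss, such as a two-sided Clopper-Pearson width of 7 points (310) or a two-sided Wald lower limit of 7% (385). The article specifies neither.
- *A reader might infer that success depends on whether 6.5% or 7% is the bound to clear.* No section makes either figure a pass/fail rule. They appear only as planning precision. The benchmark stated for the primary outcome is 10%, in the Abstract, Background and Objectives. Event-count thresholds built on 6.5% or 7% would be a reader's own construction.

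The choice between Wilson, exact or other intervals belongs in the analysis plan and is not a fault here.

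**Conclusion.** The point holds as a misstatement of the precision target. Under a Wald interval at 10%, the stated one-sided bound of 6.5% corresponds to 199 patients, and 270 delivers 7.0%. Either the 6.5% is the wrong bound, or it is a two-sided limit with the wrong label, in which case 270 is 13 patients short of the 283 needed and the interval is 0.16 points too wide. The article does not allow a choice between these.

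Severity is minor to moderate: enrolment does not change and no decision rule is affected. The statement that 298 suffices rests on the Wald formula, on a true value near 10%, and on nearly full enrolment entering the analysis. The main analysis counts all included participants, which supports the last of these. With 5% dropout, 298 × 0.95 = 283 remain, still at the largest of the three requirements. If FDG-PET-CT patients are also removed, 283 × 0.95 = 269 remain, and the two-sided width returns to about 7.2 points.

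**What to change.** Replace the two precision sentences with one that reproduces, for example: *270 evaluable patients give, at an observed proportion of 10% (27/270), a one-sided 95% lower confidence limit of 7.0% (two-sided 95% Wald CI 6.4% to 13.6%).* Delete the 6.5%, or relabel it as the approximate two-sided lower limit. If a two-sided width of 7 points was the real intention, say so and give 283 as the base number.

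Report the primary interval with the same sidedness as the sample size statement.

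Under the suggested wording, enrolment stays at 298 and the inflation steps are unchanged. The cost is restating a few figures. If 283 is taken as the base number instead, the two 5% increases need to be recomputed or the existing 298 justified against it.
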